#### Qualitative data

Thematic analyses will be conducted using an inductive approach, relying on the participant’s subjectively reported experiences and perceptions. Interview transcripts will be independently reviewed by an interdisciplinary team of coders led by expert qualitative researchers using open coding procedures. The codebook will be developed through an iterative process involving discussions between team members over code identification and application. A subset of interview transcripts will be coded independently by all members of the coding team to establish acceptable inter-coder reliability (pooled Cohen’s Kappa coefficient > 0.80), after which the remaining transcripts will be divided among the coders. Transcript excerpts will be organized into emergent key themes. Thematic saturation will be determined when no new themes are identified. Findings will be presented to a subset of participants to elicit feedback to validate thematic analyses. Debrief sessions will also be held with the research team to present findings and further validate or challenge interpretations of the data. Results will be reported in accordance with Consolidated Criteria for Reporting Qualitative Research Guidelines.

### Interim analyses {21b}

We will not conduct interim analyses.

### Methods for additional analyses (e.g., subgroup analyses) {20b}

Potential differences in treatment effects across influential participant characteristics (e.g., maternal age, number of children, infant sex) and group WCC characteristics (e.g., group size) will be assessed. A scale variable that will reflect a participant’s attendance level at group WCC visits will be created and included in the models to evaluate whether there is a “dose–response” intervention effect. Analyses will follow intent-to-treat principles, with participants analyzed according to randomized treatment assignment. In addition, a “per-protocol” analysis will be performed; the per-protocol analysis would include only participants who were adherent to their assigned study regimen and completed 75% of the recommended number of WCC sessions by 18 months of follow-up.

### Methods in analysis to handle protocol non-adherence and any statistical methods to handle missing data {20c}

The randomness of missing data between subjects and within given a subject will be investigated using available information on subject characteristics to help discern patterns in the missing data and to identify the possible missing data mechanisms (e.g., missing at random). Imputation strategies used to handle missing data will be considered as appropriate.

### Plans to give access to the full protocol, participant-level data and statistical code {31c}

Upon completion of the trial, the study protocol and de-identified participant-level data for own research purposes can be requested by submitting a research proposal to the principal investigators ([name] [[contact]] and [name] [[contact]]).

## Oversight and monitoring

The principal investigators will monitor the study to ensure that it is conducted according to the IRB-approved protocol.

### Composition of the coordinating center and trial steering committee {5d}

The trial steering committee consists of the principal investigators and all co-investigators. Team meetings occur on a monthly basis. This specified steering committee is responsible for overall oversight and governance of the trial with the final responsibility remaining with the PIs.

### Composition of the data monitoring committee, its role and reporting structure {21a}

Due to the low risk of the study, a formal data monitoring committee was not formed. There are no formal stopping rules for the trial because there are no anticipated problems that are detrimental to all participants. The principal investigators will review all data collection forms and electronic databases on an ongoing basis for data completeness and accuracy as well as protocol compliance. The research assistant will report weekly on recruitment, participants retained, and whether any issues with confidentiality or unexpected participant or data issues have arisen.

### Adverse event reporting and harms {22}

Monitoring and reporting of adverse events will be conducted from the time of consent to trial entry until the end of the trial. Adverse events and harms will be collected non-systematically, i.e., through spontaneous reporting of events. Research personnel will be asked to report unanticipated problems and adverse events, including serious adverse events such as an important medical event, hospitalization, or death of a mother or of a child of an enrolled mother, within 24 h of learning of the event. If known, the reason for the event should also be reported. The principal investigator, who is a pediatrician, will review the event within 24 h. The purpose of the review will be to assess if there is any reason that the event can be considered attributable to the study’s intervention. If the study is considered a causative factor, the report will be forwarded to the other principal investigator. The principal investigators will then determine the appropriate response through consultation with appropriate individuals. Adverse events will be documented in the participant file and reported to the appropriate IRB. It is believed that rarely would the study be considered a possible cause, but the establishment of the review procedure should assure that harm potentially attributable to the study is not missed and that any identified harm is addressed and avoided going forward. The review procedures developed for this study consist of weekly meetings with the opioid treatment program clinical team to review specific issues that were identified in the group visits. Issues such as maternal substance use or relapse, child safety concerns, and indications for child protective service involvement as well as housing, family safety, and other concerns are addressed with the team and clinical therapists, social workers, navigators, or peer support specialists are engaged to address issues.

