### Intervention description {11a}

As the framework for the group WCC intervention, we leveraged Centering®, a model of care delivery developed by The Centering® Healthcare Institute [15]. Centering® seeks to shift the paradigm of health services from individual to group care, bringing patients out of a traditional office and into a group setting where they learn from their providers and each other. Each group session has planned core content, with consistency of providers across all sessions, and 2 h per session for health assessment, interactive learning, and community building. Instead of didactic education, providers use facilitative leadership, encouraging patients to fully engage in their care and raise issues of importance to them.

*CenteringParenting*is the pediatric adaptation of Centering® and is based on the American Academy of Pediatrics recommended schedule of visit periodicity, including developmental milestone assessments, anticipatory guidance, and immunizations [16]. In addition to standard WCC topics focused on infant health and development, *CenteringParenting*places emphasis on maternal wellness including nutrition and exercise, family planning, stress reduction, and interpersonal relationships [14, 17].

Participants who enroll into CHAMPS during pregnancy and are randomized to the intervention arm initially receive routine individualized well care after birth hospital discharge. This consists of an initial 30-min newborn visit usually within 2–3 days after discharge at the affiliated pediatric primary care office, with any additional 15-min visits in the first few weeks of life as needed, i.e., for jaundice or a weight check. Beginning with the 1-month WCC visit, mother-infant dyads grouped by birth month (anticipated *n* = 3–5 per group) are scheduled for WCC together, with subsequent visits occurring at the American Academy of Pediatrics recommended intervals (2, 4, 6, 9, 12, 15, and 18 months of age). Group WCC visits occur on-site at the opioid treatment program. Infants with an extended hospitalization beyond 1 month are eligible to join into a later group session if needed.

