### Control description

Clusters randomized to the control arm receive routine individualized WCC at an urban, hospital-owned academic pediatric practice located 5 city blocks from the opioid treatment program. This practice site includes 14 physicians and nurse practitioners, serves a predominantly Medicaid-insured population, and is a training environment for students and residents. Newborns are scheduled for an initial 30-min visit within 3–5 days after discharge home, with any additional 15-min visits in the first few weeks of life as needed (i.e., for jaundice or a weight check). Subsequent 15-min WCC visits occur at recommended intervals per American Academy of Pediatrics recommendations (1, 2, 4, 6, 9, 12, 15, 18, 24, 30, and 36 months of age). Routine care in this practice setting includes maternal depression screening, provision of books as part of a national literacy promotion program, developmental screening, and social determinants of health screening. A dedicated RN coordinator tracks receipt of preventative services for all patients and provides outreach to patients who no-show for WCC, and access to subspecialty care, social work, and lactation services are available on-site. Scheduling of visits may occur in-person at the registration desk, through an online patient portal, or by telephone. Phone or text appointment reminders are provided the day before scheduled visits.

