
#### Secondary outcomes

##### Infant healthcare utilization

Data are abstracted from the child’s EMR at the end of the 18-month follow-up period, including receipt of on-time immunizations and screenings (i.e., lead, hemoglobin, and developmental assessments); infant hepatitis C screening at 18 months among those with perinatal hepatitis C exposure; the number of acute primary care visits (“sick visits”); emergency department utilization and hospitalizations; subspecialist referrals and visits (e.g., Neurology, Ophthalmology, Developmental Medicine); and early intervention referral and enrollment. The proportion of participants who receive these services within the 18-month study period will be compared between the 2 study arms. The mean number of hospitalizations and sick, emergency, and specialist visits will also be compared between the 2 groups.

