## Data collection and management

### Plans for assessment and collection of outcomes {18a}

Data is derived through EMR abstraction and from questionnaires completed during study assessment visits. Data from all sources are matched by the participant’s unique study identification number and entered into one master electronic REDCap database. Data entry and checking is an ongoing process as the data become available. The final analytic dataset will be void of personal identifiers to protect the confidentiality of participants.*Medical record abstraction*: EMR data of participants and their children are abstracted by research personnel following participant enrollment into the study, the birth of a participant’s child, and at the 6-, 12-, and 18-month study visits. A standard data abstraction form is used.*Participant assessments*: All randomized study participants in both study arms will have a total of 5 assessment visits with research personnel. The first visits will occur immediately following enrollment into the study (baseline). For participants who enroll while pregnant, subsequent study assessment visits will occur prior to the participant’s child turning 1 month of age, and within 4 weeks of the participant’s child turning 6, 12, and 18 months of age. For participants who are not pregnant when they enroll, subsequent study assessment visits will occur at 1, 6, 12, and 18 months post-enrollment. At each assessment visit, participants will complete a set of standardized questionnaires in a private research room using traditional paper-and-pencil forms. No personally identifying information will be collected on the questionnaires. The 18-month study visit will also involve a 15-min observed free play session between the mother and child, which will be videotaped and subsequently coded according to standardized procedures using the *Keys to Interactive Parenting Scale* [23].*In-depth interviews*: Participants in the intervention arm will participate in semi-structured, individual in-person interviews at 9 and 18 months after their first group WCC session. These interviews will be conducted in a private research room, last 20–30 min, and be audio recorded and transcribed verbatim by a HIPAA compliant transcription service. During the session, participants will be asked to discuss things that they like and dislike about the group WCC program and how the program could be improved. Participants will be asked to report their experiences of receiving care in a group format, focusing on session structure, interaction with other mothers, and receiving specific information. Standardized interview question guides with prompts to engage participants in a fluid discussion will be used.

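### Harms are collected only by spontaneous report, and the standing review draws on group visits that only one arm has, so events are liable to be found unequally

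*Protocol article*

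**What the plan says.** The protocol article, Adverse event reporting and harms {22}, makes a positive choice of method: "Adverse events and harms will be collected non-systematically, i.e., through spontaneous reporting of events". Research personnel must report serious events in mothers and children "within 24 h of learning of the event". A principal investigator then reviews each reported event for a link to the intervention. The section goes on to say what the study's review procedures consist of: "weekly meetings with the opioid treatment program clinical team to review specific issues that were identified in the group visits". It gives the purpose as follows: "the establishment of the review procedure should assure that harm potentially attributable to the study is not missed".

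The two arms receive care in different places. Intervention description {11a}: "Group WCC visits occur on-site at the opioid treatment program". For the other arm, the section headed Control description has: "Clusters randomized to the control arm receive routine individualized WCC at an urban, hospital-owned academic pediatric practice located 5 city blocks from the opioid treatment" (quotation cut one word before its end).

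Some data are collected alike in both arms. Under Plans for assessment and collection of outcomes {18a}, every participant has five assessment visits, and "EMR data of participants and their children are abstracted by research personnel following participant enrollment into the study", with further abstraction at birth and at the 6-, 12- and 18-month visits. Infant healthcare utilization takes the child's "emergency department utilization and hospitalizations" from the record as a secondary outcome. Maternal illicit substance use takes urine screens from the treatment program's records, also as a secondary outcome.

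**The concern.** With spontaneous reporting, an event is counted only if someone tells the research team or the team comes across it. How often that happens depends on how closely participants are watched. Here the closer contact belongs to one arm: long group sessions co-led by a treatment program nurse practitioner, a weekly meeting about what those sessions bring up, and two interviews. Section {17a} indicates that an investigator delivers the group care, so the study hears of problems there at first hand. Controls see the staff of a separate practice, and the article describes no duty for those staff to tell the study about events.

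Two things are at stake. A count of events by arm would mix true harm with intensity of observation. And serious events in control mothers, or safety concerns in control families, might not reach the review that is meant to make sure harm is not overlooked. The trial is open label ({16b}) and has no data monitoring committee ({21a}), so no independent body would be placed to notice such an imbalance.

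**Working it through.** The article states no harms figure, so there is nothing to reproduce. The check sets the routes to an event side by side.

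| Route | Intervention | Control | Stated link to adverse event reporting |
|---|---|---|---|
| Group visits ({11a}) | 8 sessions of 2 h for a dyad enrolled in pregnancy | none | feed the weekly meeting ({22}) |
| Interviews ({18a}) | 9 and 18 months after first session | none | none |
| Individual well child visits | newborn visits, and after a missed group visit | 15 min, at the same ages | none |
| Assessment visits ({18a}) | 5 | 5 | none; no event question described |
| Record abstraction, mother and child ({18a}) | yes | yes | none |
| Child hospital and emergency use | yes | yes | none; secondary outcome |
| Maternal urine screens | yes | yes | none; secondary outcome |
| Weekly research assistant report ({21a}) | yes | yes | covers unexpected participant issues; no enquiry described |

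**Contact.** For a dyad enrolled in pregnancy, the scheduled visits at 1, 2, 4, 6, 9, 12, 15 and 18 months number 8.
- Intervention: 8 × 2 h = 16 h, shared among an anticipated 3 to 5 dyads, with study-linked clinicians.
- Control: 8 × 15 min = 120 min = 2 h, with practice clinicians.

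These hours show that contact differs. They do not measure detection.

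**Timing.** The longest gap between group visits is 3 months (for example 9 − 6). The longest gap between assessment visits or abstractions is 6 months (12 − 6, or 18 − 12). The reporting clock starts when staff learn of an event. A control mother's hospitalization found only at abstraction could therefore be reported about 6 months after it happened and still meet the rule.

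**Size.** Let p be the true proportion with an event, equal in both arms, and d the probability that an event is found. The apparent risk ratio is (p × d_I) / (p × d_C) = d_I / d_C. The article gives neither p nor d, so these values are assumptions:
- 0.9 and 0.9: 1.00
- 0.7 and 0.6: 1.17
- 0.8 and 0.6: 1.33
- 0.9 and 0.5: 1.80

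With 54 per arm and an assumed p of 0.20, the last pair gives 54 × 0.20 × 0.9 = 9.7 recorded against 54 × 0.20 × 0.5 = 5.4. Each ratio is simply the assumed detection ratio. The list shows the mechanism and is not an estimate for this trial.

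**Against the section's own aim.** The section relies on its review procedure so that harm is not missed. The principal investigator's review covers both arms but acts only on events already reported. The one recurring procedure in that section that brings problems to light has no counterpart in the control arm.

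**The case against.** The case on the other side is substantial, and much of it stands.

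- No comparison of harms by arm is planned, either among the outcomes or in the statistical methods. The stated purpose of review is to judge, case by case, whether an event is attributable to the intervention. Closer watch on the arm that receives the intervention fits that purpose. This stands, so the point concerns any by-arm summary that may be made, not an analysis already specified.
- A reader might infer that control mothers have no source for hospitalization or death. The article does not support that. Abstraction covers mothers in both arms, and research personnel who saw such an event there would have to report it. What is missing is a statement that abstraction feeds the event log.
- A reader might also infer that the weekly meeting inflates the intervention arm's event count. The section says that problems raised there are taken up with clinical and support staff. It does not say that they are logged as adverse events.
- Controls are not out of sight. All participants are patients of the same treatment program. The control practice screens for maternal depression and social needs and follows up missed visits. Maternal depression, stress and urine screens are measured in both arms, so relapse has a source common to both.
- The trial is low risk, and a journal article need not list form fields.

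What remains is that the article chooses non-systematic collection in so many words, and never says that the contacts common to both arms are used to find events.

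**Conclusion.** The concern holds as a liability to unequal detection. It does not show a bias that has occurred. Spontaneous collection, together with a standing review fed from one arm, makes it likely that events are noticed more readily in the intervention arm. This applies most to serious events in mothers and to child or family safety concerns. It applies less to the child's hospital and emergency use and to maternal drug use, which are measured in both arms as outcomes.

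The size cannot be computed from the article. A reader might take from the illustration that the harms result is distorted by a factor of up to 1.80; nothing in the article supports that or any other figure. The direction rests on one assumption, that more contact with study-linked clinicians means more events become known to the study. The primary outcomes and their analysis are not affected. This is a worthwhile, low-cost improvement to safety data collection.

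**What to change.** In Adverse event reporting and harms {22}, replace spontaneous-only collection with scheduled collection that is the same in both arms. Keep the existing 24 h reporting duty for events learned of in between.

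1. Ask one fixed event question, in the same words, at each assessment visit.
2. Read hospitalizations and deaths of mothers and children from the abstraction already planned at 6, 12 and 18 months, and enter them in the adverse event log.
3. Record the source of every event. Base any harms summary by arm on the common sources in items 1 and 2.
4. List separately the events known only through group visits, the weekly meeting or the intervention-arm interviews, and leave them out of any comparison between arms.

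This takes a few fields on existing forms and a short change to the section, with no new visits or staff. The small downside is more events to log and review. Because the trial is open label, answers to the fixed question may still differ somewhat by arm. Events taken from the record do not depend on what participants choose to report.

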### Frequency and plans for auditing trial conduct {23}

Regular meetings (weekly/monthly) will be held to monitor the study conduct and address potential problems.

### Plans for communicating important protocol amendments to relevant parties (e.g., trial participants, ethical committees) {25}

Changes to the protocol will be communicated to the IRB and approval from the IRB will be obtained prior to implementing any proposed changes.

### Dissemination plans {31a}

Trial results will be disseminated at local and national conferences and submitted for publication in peer-reviewed journals.

## Discussion

Given the current opioid epidemic and the increase in opioid use and misuse among pregnant women in the USA, this project is timely and highly relevant. The integration of group WCC into maternal OUD treatment represents a “game-changer” in disrupting health system silos and addresses the intergenerational effects of maternal OUD by improving parenting and engagement in and experience of preventative care. Findings from this work will be critical to informing implementation at a national scale.

## Trial status

Trial recruitment began on December 30, 2021. It is expected that recruitment will end in 2023.

